#### Randomization

The participants eligible for enrolment will be randomized in a 1:1 ratio to Ashwagandha + COVISHIELD^TM^ or placebo + COVISHIELD^TM^ according to a pre-specified randomization scheme prepared by a statistician (SS) using a computerized system. Block randomization specific to each clinical study site will ensure equal number of participants per group with a small block size (e.g., a block of 4–6 participants). The statistician (SS) will design the randomization schedule following computer generated random numbers. The randomization scheme will consider the subsets of participants who are receiving first and second dose.

The patient number and the treatment allocation as per the schedule will be printed on a card, which will be sealed in an opaque envelope for each patient. The envelope of each patient will be delivered to respective trial sites. The treatment allocation will be concealed. Considering the study design, it is important to have a dosage form that ensures blinding. The tablets of Ashwagandha and placebo will have identical color and weight and will be dispensed in sealed bottles. The bottles will have same color and labeling. The bottles will be specific to the participant. The participant code will be written on each bottle containing the tablets.

#### Monitoring

Following randomization at baseline, participants will be physically checked by study physicians at all visits till the completion of study. At all the time points, assessment of participants will also include in-depth inquiry of possible symptoms of COVID-19 in family members and close associates. The participants will be provided with a user friendly mobile app (named COVID Kavach) designed for COVID-19 studies for daily tracking and monitoring of onset of fever/ respiratory and any other symptoms/vaccine related side effects (18). The daily response of the participant will be seen by the site physician and study co-ordinators; anonymous participant data which will only be identified by a unique study ID known to the site investigator will be saved in a dedicated central study server. In addition, a telephonic contact will be made by the site coordinator with the participant once in every 2 weeks till study completion to find out about any matter concerning health or the study. The schedule of enrolment, interventions, and assessments is provided in Table 3.

**Table 3 T3:** Schedule of enrolment, interventions, and assessments.

	**Study period**							
	**Enrolment**	**Allocation**	**Post-allocation**					**Close-out**
**Timepoint**	* **D** * _ **−07to −01** _	* **D** * _ **01** _	* **W** * _ **04** _	* **W** * _ **08** _	* **W** * _ **12** _	* **W** * _ **16** _	* **W** * _ **24** _	* **W** * _ **28** _
**Enrolment**:								
Eligibility screen	X							
Informed consent	X							
Allocation		X						
**Interventions***:								
[Daily dosing of placebo or Ashwagandha]								
**Assessments**:								
Concomitant illness	X	X	X	X	X	X	X	X
Randomization		X						
Complete physical examination	X	X	X	X	X	X	X	X
WHO QOL BREF, HR-BHF		X			X		X	X
Vital signs	X	X	X	X	X	X	X	X
Ayurvedic phenotype: prakriti		X						
Ayurvedic assessment: dhatu sarata, srotasa pariksha		X	X	X	X	X	X	X
ECG, Chest-X ray	X						X	
Study drug dispensation,		X		X		X		
Compliance			X	X	X	X	X	X
Mobile App–Kavach–self reported questionnaire								
Blood hemoglobin, total and differential count, platelets, ESR, SGOT, SGPT, alkaline phosphatase, serum albumin, globulin, bilirubin, blood urea nitrogen, serum creatinine,	X				X		X	
D-dimer	X				X		X	
HbA1c, blood sugar fasting, urine routine	X				X		X	
Urine pregnancy test	X		X	X	X	X	X	X
RT-PCR throat/nose swab testing for SARS-CoV2 RNA	X		X	X	X	X	X	X
SARS- CoV-2 S1, RBD and N Specific IgG		X	X	X	X	X	X	X
sVNT					X		X	X
SNT (variants-USA-WA1/2020 and Lineage B.1.617.2; delta variant)					X			X
Completion and outcome report								X
AE								

*Additional studies on measurement of secretory IgA and T cell responses are planned on a subset of the participants*.

#### Compliance

The participants will be daily monitored for fever, respiratory and any other symptoms and vaccine related side effects. Telephonic follow up will be done once in every 2 weeks throughout the study. The study coordinator will contact the participants for monitoring symptoms and ensure compliance. Medication logs will be maintained for both vaccine use and Ashwagandha tablet consumption. On each return visit, the participant will be instructed to bring all unused medication and a tablet count will be performed and recorded in the medication log. COVID-Kavach App and regular telephonic contact will be used to remind participants to adhere to study medication instructions.

#### Trial Intervention

The study includes two arms as Ashwagandha and Placebo The participants from placebo arm will have immunogenic effects only of vaccine, whereas participants in Ashwagandha arm may have additional safety, immunogenicity and protection from disease. Thus, the placebo arm will serve as a control to ascertain adjuvant effects offered by Ashwagandha.

Arm 1: Ashwagandha tablets (*n* = 600): Dose of Ashwagandha prescribed for this study is one tablet of the standardized aqueous extract equivalent to 4 gm Ashwagandha root powder per day administered within 7 days of the first or second dose of vaccine and continued up to 24 weeks. Each tablet used in this trial shall contain aqueous extract equivalent to 4 grams Ashwagandha root powder.

Arm 2: Placebo (*n* = 600): One placebo tablet will be administered daily beginning within 7 days of the first or second vaccine dose and continued up to 24 weeks. The appearance and weight of placebo tablet (containing microcrystalline cellulose) will be same as that of Ashwagandha tablet.

One tablet of Ashwagandha or placebo will be administered daily (on empty stomach in the morning) with water. Quality of Ashwagandha roots is ensured in accordance with prescribed pharmacopeia standards (19).

A window period of 7 days will be allowed on either side of the scheduled visit for exceptional or any other anticipated reasons at the discretion of the investigator.

#### Clinical Outcomes

##### Primary Outcome Measure

Immunogenicity as measured by SARS-CoV-2 spike (S1) and RBD-specific IgG antibody titres.

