## Introduction

Vaccines have emerged as the most effective tool in the fight against COVID-19. Governments all over the world have rolled out COVID-19 vaccine program for their populations. Clinical studies on vaccine efficacy suggest a role of high neutralizing antibody titers, robust CD8+ and Th1-biased CD4+ responses in protection against SARS-CoV-2 infection and also break through infections (1–4). With the emergence of new variants of concern, persistence of vaccine induced humoral and cell mediated immune response is being considered as key to fight against pandemic. There is ongoing global research on further enhancing the effectiveness of existing vaccines either by developing new vaccines against variants or by booster vaccination (5).

Botanical immunomodulators especially those based on traditional medicine offer opportunities for combined use with vaccines to induce optimum and persistent host immune responses (6). *Withania somnifera* (WS) also known as Ashwagandha in Ayurveda is a widely used medicinal plant for its immunomodulatory properties. Various studies on Ashwagandha have established its use as an immune-adjuvant in infection, inflammation and diseases such as arthritis and cancer (7). Immunoadjuvant activity of Ashwagandha has been reported in an infection model when co-administered with DPT (diptheria, pertussis, tetanus) vaccine (8). The long-term safety of Ashwagandha is well documented (9–13). It is also being investigated in comparison with hydroxychloroquine in a randomized controlled multi-centric clinical study for its prophylactic activity against COVID-19 in high-risk health care workers (CTRI/2020/08/027163, CTRI/2020/05/025332).

Based on our earlier studies, we hypothesize that co-administration of Ashwagandha with COVID-19 vaccine may result in better safety, immunogenicity and protection. Further, the vaccine efficacy, 22–90 days after a single dose of ChAdOx1 has been reported to be 76% (14). In this context it would be interesting to investigate whether Ashwagandha co-administration is able to provide a better immune response particularly after the first dose of the vaccine.

The primary hypothesis is that a long-term administration of Ashwagandha along with COVISHIELD^TM^ vaccine leads to a better protection against COVID-19 in healthy populations as compared to COVISHIELD^TM^ vaccine alone in terms of augmented immune-response, reduced incidence of breakthrough SARS-CoV-2 infections, good safety and tolerance.

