# *HR-BHF: Health Related-Habits, Behavior and Fitness*.

@ *WHO QOL BREF: World Health Organization Quality of Life Instruments-short form*.

**Table 2 T2:** Schedule of laboratory investigations.

**Visit**	**Visit 0 Screening (Day −7 to −1)**	**Visit 1 Enrollment and randomization (Day 1)**	**Visit 2 (4 wks)**	**Visit 3: (8 wks)**	**Visit 4 (12 wks)**	**Interim analysis**	**Visit 5:(16 wks)**	**Visit 6** **Intervention completion** **(24 wks)**	**Visit 7: Part 1 completion (28 wks)**
CBC: blood hemoglobin, total and differential count, platelets Erythrocyte sedimentation rate (Westergren)	X				X			X	
D-dimer	X				X			X	
LFT: serum liver enzymes-SGOT, SGPT, alkaline phosphatase Serum albumin, globulin, bilirubin	X				X			X	
RFT: blood urea nitrogen Serum creatinine	X				X			X	
Blood sugar profile (BSL fasting and HbA1c)	X				X			X	
Urine routine	X				X			X	
^+^Urine pregnancy test	X		X	X	X		X	X	X
^#^RT-PCR throat/nose swab testing for SARS-CoV2 RNA	X		X	X	X		X	X	X
SARS- CoV-2 S1, RBD and N Specific IgG		X	X	X	X		X	X	X
sVNT					X			X	X
SNT (Wuhan isolate USA-WA1/2020 and Delta variant B1.617.2)					X				X

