# *RT-PCR throat nose swab test will be repeated in participants in case of development of any symptoms during the study duration*.

+ *for female participants*.

*Additional studies on measurement of secretory IgA and T cell responses are planned on a subset of the participants*.

If the vaccinated individual (after first or second dose) contracts COVID 19, then he/she shall be withdrawn from the study and will be treated under the supervision of COVID-19 physician till recovery. The participants who are withdrawn prematurely will be encouraged to continue follow up in a separate group as per the discretion and supervision of the study physician. The latter group will be permitted to use the current protocol methods and analyzed separately. All participants will be monitored for safety, immune response and occurrence of any breakthrough SARS-CoV-2 infection. An interim analysis at the end of 12 week is planned to evaluate the effect of Ashwagandha co-administration on safety and immune response following the first dose of the vaccine. The final analysis of data will be carried out after all the participants have completed the study at the end of 28 weeks.

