Previous clinical studies have highlighted the role of humoral as well as cell-mediated immune responses in recovery from SARS-CoV-2 infection (26, 27). In previous studies the selective-Th-1 upregulating activity of Ashwagandha was demonstrated and in infection models, co-administration of Ashwagandha with DPT vaccine resulted in improved antibody titres against lethal challenge of pertussis toxins (8). *In silico* network ethnopharmacological investigations also suggest the ability of bioactive compounds of Ashwagandha to modulate immune pathways involved in innate and adaptive immune responses (28, 29). Further, the interim efficacy data for ChAdOx1 nCoV-19, evaluated in four trials across UK, Brazil and South Africa shows a protection of 64.1% after one standard dose (14). COVISHIELD^TM^ has been administered in two doses to a large population in India. We hypothesize that co-administration of Ashwagandha with the COVISHIELD^TM^ vaccine may enhance the antibody titres particularly after the first dose of the vaccine. A sustained long-term immune response to the vaccine has implications for prevention of reinfection. Therefore, the effect of Ashwagandha on the sustenance of neutralizing antibody titres up to 4 months after the second dose will also be evaluated in this study (30). Ashwagandha is also known to improve overall mental wellbeing.

Currently, the study involves the assessment of neutralizing antibodies against two well-characterized variants of concern (B1.617.2 and USA-WA1/2020 variants). Recently, a new variant B.1.1.529, named Omicron has emerged and it is likely that other newer variants may emerge during the course of the study. It would be interesting to evaluate the responses to these variants. As and when fully characterized BEI resources are available for new variants of concern, the investigators will take the decision to modify and make the necessary amendments to the protocol. Serum samples are being preserved at all time points of the study and may be used for such additional studies.

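### Undetected and prior infections stay in the S1/RBD titre comparison, the handling of detected infections is not reconciled with ITT, and the serial N-IgG has no stated use

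*Protocol article*

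**What the plan says.** **Outcome and its reading.** Under Primary Outcome Measure the article gives "Immunogenicity as measured by SARS-CoV-2 spike (S1) and RBD-specific IgG antibody titres". Under Analysis, titres are log-transformed, geometric means are reported, and arms are compared by standard two-group tests in ITT and per-protocol sets. Trial Intervention says the placebo arm's immune effects come from the vaccine alone, and makes that arm the control for the adjuvant effect. The primary hypothesis (Introduction) also expects "augmented immune-response, reduced incidence of breakthrough SARS-CoV-2 infections, good safety and tolerance".

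**Infection.** The Discussion says natural infection produces spike IgG and notes that "Recently, a new variant B.1.1.529, named Omicron has emerged". Recruitment began in December 2021. The listed inclusion criteria ask for a negative RT-PCR and set no serological condition.

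**Detection and handling.** In Table 2, the row "RT-PCR throat/nose swab testing for SARS-CoV2 RNA" is marked at screening and weeks 4, 8, 12, 16, 24 and 28. A table note adds: "RT-PCR throat nose swab test will be repeated in participants in case of development of any symptoms during the study duration". Study Design states: "If the vaccinated individual (after first or second dose) contracts COVID 19, then he/she shall be withdrawn from the study". Withdrawal Criteria says the same of participants with a positive RT-PCR or clinical symptoms. Of withdrawn participants who continue follow-up, Study Design says: "The latter group will be permitted to use the current protocol methods and analyzed separately".

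**N-IgG.** The Table 2 row "SARS- CoV-2 S1, RBD and N Specific IgG" is marked at Day 1 and all six later visits. The Introduction says the vaccine carries the spike gene. No outcome or analysis sentence in the article uses N-IgG.

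**The concern.** S1 and RBD IgG respond to infection as well as to vaccination, so the measured titre mixes the two. Reading placebo titres as vaccine effect alone holds only if nobody in that arm has been infected, yet the trial counts breakthrough infections as an outcome.

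Three groups matter:

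- **Infections that swabs and symptoms miss.** These participants stay in with boosted titres.
- **Infections before entry.** Randomisation balances these in expectation, but they add spread.
- **Detected infections.** The article withdraws these participants and analyses those who continue separately, but also promises ITT. It does not say whether their later titres count in the primary comparison.

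If treatment lowers infection, placebo holds more boosted titres and a true enhancement looks smaller. Withdrawal also depends on an event that treatment is meant to change. If those who become infected tend to have low titres (an assumption), removing them raises the placebo mean and biases in the same direction. If treatment leaves infection unchanged, the cost of retained infections is power.

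The article also hopes to show a late rise in response (Strengths and Limitations). For the at least 900 second-dose participants no further dose is described, so infection is a rival explanation of such a rise.

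**Working it through.** **The plan's own figure.** The article gives no titre SD, infection rate or size of infection boost, so it has no figure on this point. Its sample size reproduces as a calculation on proportions: 2 × 0.8 × 0.2 × (2.176 + 0.842)² / 0.07² ≈ 595 per arm, rounded to 600. This takes the 7% as absolute and alpha as 2.96% two-sided, which the article states only for the interim analysis. It says nothing about titres.

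**Step 1: asymptomatic infections missed by scheduled swabs.** There are six swabs in 28 weeks (196 days). Assume infection times are uniform and RT-PCR stays positive for D days. Share caught = 6 × D / 196.

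| D (assumed) | Caught | Missed |
|---|---|---|
| 7 days | 42/196 = 0.21 | 0.79 |
| 10 days | 60/196 = 0.31 | 0.69 |
| 14 days | 84/196 = 0.43 | 0.57 |
| 21 days | 126/196 = 0.64 | 0.36 |

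Symptom-triggered swabs do not change this for infections without symptoms.

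**Step 2: bias.** Let q be the share of placebo participants with an infection retained in the titre data, RR the infection risk ratio (Ashwagandha/placebo), and F the fold boost from infection. All three are assumptions.

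Bias in log10 GMT ratio = q × (RR − 1) × log10 F; multiplier = 10^bias.

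| q | RR 1, any F | RR 0.7, F 5 | RR 0.5, F 3 | RR 0.5, F 5 | RR 0.5, F 10 |
|---|---|---|---|---|---|
| 5% | 1.00 | 0.976 | 0.973 | 0.961 | 0.944 |
| 10% | 1.00 | 0.953 | 0.947 | 0.923 | 0.891 |
| 20% | 1.00 | 0.908 | 0.896 | 0.851 | 0.794 |

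Example: 0.20 × (−0.5) × 1 = −0.10, and 10^−0.10 = 0.794. The ratio can cross 1: at q = 30%, RR 0.7, F 5 the multiplier is 0.865, so a true ratio of 1.15 becomes 0.995.

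**Step 3: variance.** Added log10 variance = q(1 − q)(log10 F)². At q = 20%, F = 5: 0.16 × 0.489 = 0.078. That is +49% on an assumed SD of 0.4 (variance 0.16) and +22% on 0.6 (variance 0.36).

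**Step 4: power.** Assume a true ratio of 1.20 (log10 = 0.0792), SD 0.4, F = 5, 600 per arm and alpha 0.0296 two-sided. The placebo-arm variance is used for both arms, a small simplification.

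| q | RR 1 (variance only) | RR 0.7 (variance and bias) |
|---|---|---|
| 0 | 0.895 | 0.895 |
| 5% | 0.848 | 0.727 |
| 10% | 0.805 | 0.523 |
| 20% | 0.737 | 0.197 |

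Example, q = 10%, RR 1: variance 0.16 + 0.09 × 0.489 = 0.204, SD 0.452, standard error 0.452 × √(2/600) = 0.0261; 0.0792 / 0.0261 = 3.04; less 2.18 leaves 0.86, so power is 0.805.

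**The case against.** The strongest reply is that the article condenses a full protocol. Covariates, rules for intercurrent infection and sensitivity analyses commonly sit in that protocol or in the SAP, neither of which is shown. The missing N-IgG rule is therefore weak evidence on its own. This stands, and the point does not rest on that absence. It rests on what the article does state: placebo titres are attributed to vaccine alone, and withdrawal with separate analysis sits beside ITT.

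A reader might infer that the trial cannot tell vaccine enhancement from infection at all. The document does not support that. Participants with a positive RT-PCR or clinical symptoms are withdrawn and analysed separately. A daily app, fortnightly calls and repeat swabs on symptoms support detection. The secondary outcomes also mention evidence of infection before vaccination, though the wording is unclear. What remains is undetected infection, prior infection and the unclear treatment of detected infections under ITT.

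A reader might also infer that a positive titre result would be an artefact of infection. As a systematic effect that would need more retained infection on Ashwagandha, and nothing in the document suggests it. The mechanism here runs against Ashwagandha, and only if treatment lowers infection risk. Nor do the two parts of the hypothesis contradict each other: titres and infections are separate outcomes. They interact only through retained infections.

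Finally, every magnitude input is assumed, and Step 2 treats all retained infections as preceding the titre analysed. That also stands.

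**Conclusion.** The concern holds in limited form. The primary comparison is read as vaccine response although undetected and prior infections remain in it, and the article leaves open whether titres after a detected infection count.

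With no treatment effect on infection, expected bias is zero and the cost is precision: power falls from 0.895 to 0.805 at 10% retained infection under the Step 4 assumptions. With a protective effect the GMT ratio is also pulled down. For q up to 20%, RR 0.5 to 1 and F 3 to 10, the multiplier runs from 1.00 to about 0.79; larger q would lower it further. The document settles the direction under that condition but not the size. The point merits a change to the analysis plan and does not invalidate the primary outcome.

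**What to change.** 1. Keep the all-randomised titre comparison as primary. State whether titres after infection count in it, and reconcile the withdrawal and separate-analysis text (Study Design, Withdrawal Criteria) with ITT (Analysis). Amend the statement that placebo titres reflect vaccine alone.
2. Adjust the log-titre comparison for Day-1 N-IgG status and Day-1 titre, and report results by Day-1 N-IgG status.
3. Pre-specify a supplementary longitudinal analysis. Treat titres from the first positive RT-PCR or first N-IgG rise onward as affected by infection and set them to missing. A rise means seroconversion, or a defined fold-rise in those N-positive at Day 1, whom seroconversion alone cannot flag. State the missing-at-random assumption and add a sensitivity analysis for it.
4. Report RT-PCR- and N-IgG-defined infection by arm beside the titre results.

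Do not require the two titre analyses to agree in direction before claiming enhancement. The all-randomised result is the one that protection would pull down, so such a rule would keep that bias.

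The cost is plan wording, one extra model and its sensitivity analysis. No new samples are needed, because N-IgG is already scheduled at every titre visit. The supplementary analysis conditions on a post-randomisation event, and missingness may depend on titre if low responders are infected more often. It therefore supplements ITT and does not replace it.

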##### Secondary Outcome Measures

Safety as measured by occurrence of adverse events. Protective immune response as measured by SARS-CoV-2 specific neutralizing antibody titer; Duration of sustenance of SARS-CoV-2 virus neutralizing antibody titer; percent seroconversion after each vaccine dose; number of participants with SARS-CoV-2 breakthrough infections; proportion of participants with COVID 19 (RT PCR assay confirmed) after the first dose and both showing evidence of infection before vaccination (Time frame: Day 1 vaccination to Week 12 or second dose and whichever is earlier); proportion of participants with COVID-19 (RT-PCR assay confirmed) after completion of the second dose (Time frame: Second dose to week 28 or study completion) and Quality of life measured using standard WHO Quality Of Life-BREF 1997 (20) and recently designed and validated Health Related-Behavior Habit Fitness (CRD Pune version 2020) questionnaires. All clinical and laboratory investigations and assessments pertaining to general health, and to rule out concurrent medical illness including COVID-19 will be carried out as per Tables 1, 2.

